### Ethical Aspects and Data Confidentiality

The present study follows national and international regulations, including the Declaration of Helsinki Ethical Principles for Medical Research Involving Human Subjects, Good Research Practice principles and guidelines, and the *Real Decreto 957/2020, de 3 de noviembre*, which regulates observational studies of medicines for human use. The study protocol was approved by the Institut Universitari d’Investigació en Atenció Primària Jordi Gol Clinical Research Ethics Committee, the reference institution for research in primary health care of the ICS, on September 27, 2022. In accord with Spanish legislation on confidentiality and data protection (*Ley Orgánica 3/2018, de 6 de diciembre de 2018, de Protección de Datos Personales y garantía de los derechos digitales*), data included in SIDIAP are always pseudoanonymized. Thus, it is not necessary to obtain informed consent from the participants.

## Results

We expect to describe the epidemiology of UTIs in Catalonia during the period from 2012 to 2021, including the characteristics of the population, diagnoses of UTI, the use of urine cultures or laboratory tests, and different antibiotics prescribed according to treatment guidelines for dose and duration. Furthermore, we will report the degree of adequacy of the prescribed treatments and the clinical evolution of the patients (ie, the rates of clinical resolution, recurrence, hospitalization, and complications, such as acute pyelonephritis, urosepsis, pneumonia, COVID-19, and death).

The first phase of the ITUCAT project is expected to be completed during the second half of 2023. Phase 2 will start after the data from phase 1 are obtained and used to create the predictive scale for acute pyelonephritis in patients with UTI; phase 2 is expected to be completed in 2024. Phase 3 will be carried out during the second half of 2023 and during 2024 to evaluate the degree of inadequacy in requests for urine cultures according to the clinical practice guidelines and establish the basis for a training intervention.

The results obtained will be presented according to the Reporting of Studies Conducted Using Observational Routinely Collected Health Data Statement for Pharmacoepidemiology (RECORD-PE) recommendations [42].

## Discussion

We expect to find inadequate management in a high percentage of UTI cases, considering that on many occasions patients are treated with second- or third-line antibiotic therapies with a preference for the longest regimens. Likewise, the use of suppressive antibiotic therapy as a prophylaxis in cases of recurrent UTI is expected to vary in our study.

In addition, we aim to determine whether women with recurrent UTIs treated with antibiotic suppressive therapy have a higher incidence and severity of potentially serious future infections, with special attention to acute pyelonephritis, urosepsis, COVID-19, and pneumonia, in comparison to women who are treated with antibiotics only when they present with a UTI.

All the information obtained in this first phase will allow us to continue with the following WPs of the project. Furthermore, if we find the inappropriate use of antibiotics, we will work on the creation of proposals to promote the correct treatment of UTIs in our environment according to clinical guidelines [40,41]. In this way, we will promote responsible management of UTIs in PHC among health care personnel and patients. In addition, our study will provide valuable information for health care policy makers and national programs to optimize the use of antimicrobials.

Because this is an observational study based on data from administrative databases, it will not allow causality analysis. However, the results will be derived from health care carried out under conditions of routine clinical practice with data from electronic primary-care registries, including the SIDIAP, CMBD-HA, and CMBD-UR databases, which have proven to be valid and representative of the population in numerous previous studies [31,34,35]. Some limitations of these studies arose from underreporting of some variables and diagnoses that we will try to avoid with the use of the different databases. Another limitation of the databases is the lack of links between diagnoses and treatments. In order to deal with bias from this specific limitation, we plan to use proxy values available in the databases, such as dates of prescriptions and dates of diagnoses. An inherent limitation of observational studies is the presence of unmeasured confounding variables. A complete adjustment for all possible confounders would require detailed information on clinical parameters, lifestyles, socioeconomic conditions, use of over-the-counter medications, and personal circumstances, which is not routinely present in electronic health records, causing residual confounding bias. Nevertheless, this bias would affect all included populations equally. To minimize confounding, we will conduct sensitivity analyses and use external adjustments or specific statistical methods when appropriate [43]. We will also take this aspect into account in the scientific discussion of the results, as it is an inherent limitation of studies conducted with electronic health records.

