**Conclusions:**

We expect to find a high percentage of UTI cases with inadequate management according to the national guidelines, considering that on many occasions UTIs are treated with second- or third-line antibiotic therapies with a preference for the longest regimens. Furthermore, the use of antibiotic suppressive therapies, or prophylaxis, in recurrent UTIs will likely be highly variable. Moreover, we aim to determine whether women with recurrent UTIs treated with antibiotic suppressive therapies have a higher incidence and severity of potentially serious future infections, with special attention to acute pyelonephritis, urosepsis, COVID-19, and pneumonia, compared to women who receive antibiotic treatment after they present with a UTI. This is an observational study of data from administrative databases that will not allow causality analysis. The limitations of the study will be handled according to the appropriate statistical methods.

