### Statistical Analysis

Demographic and baseline characteristics of the participants will be reported as frequencies and percentages for categorical variables and means and standard deviation or median and interquartile range for continuous variables, as appropriate.

For WP 1, descriptive statistics will be reported for the results. For WP 2, a severity variable will be constructed that will include mortality and hospitalization, in addition to the presence of pneumonia in cases of COVID-19. Quantitative variables will be described as means and standard deviation, while categorical variables will be described as the proportion of exposed and unexposed individuals. Univariate tests will include the Student *t* test and the chi-square test, as appropriate. For the primary outcome, marginal structural models will be fitted to estimate causal effects by correcting for confounders. Inverse probability weights will be estimated as a function of propensity score using sociodemographic variables and clinical variables. The inverse probability weights will be used in the marginal structural model to estimate the risk ratio and confidence intervals for the prevalence of each outcome among individuals exposed to antibiotics versus those not exposed to antimicrobials. During the assessment of the correlation of prior antibiotic exposure with the different outcomes, patients will only be counted once and assigned to the worst outcome (with the severity of COVID-19 ranked in decreasing order as death, hospitalization, and pneumonia). The Wald test will be used to determine whether the adjusted risk ratios are significantly different from zero at a significance level of 5%.

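### The article says residual confounding would affect all populations equally, which cannot hold for the WP 2 risk ratio, and it both claims and disclaims causal estimation

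*Protocol article*

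**What the plan says.** The limitations paragraph of the Discussion makes three statements in sequence. It concedes the problem: "An inherent limitation of observational studies is the presence of unmeasured confounding variables". It explains that full adjustment would need information "which is not routinely present in electronic health records, causing residual confounding bias". It then offers an assurance, with no argument or data behind it: "Nevertheless, this bias would affect all included populations equally". The next sentence promises mitigation: "To minimize confounding, we will conduct sensitivity analyses and use external adjustments or specific statistical methods when appropriate".

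The comparison this bears on is set out in the secondary end points and again in the Discussion. It is between women with recurrent infections on suppressive therapy and women with recurrent infections treated episode by episode. The Statistical Analysis section plans inverse probability weights from a propensity score built on sociodemographic and clinical variables. It gives the purpose of the weighted models for the primary outcome as follows: "marginal structural models will be fitted to estimate causal effects by correcting for confounders".

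Two other places say the opposite about what can be learned. The Abstract (Conclusions) states: "This is an observational study of data from administrative databases that will not allow causality analysis". The Discussion states: "Because this is an observational study based on data from administrative databases, it will not allow causality analysis".

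**The concern.** Confounding of a between-group ratio exists only when a risk factor is distributed differently in the groups. To say that residual confounding is present and also falls equally on everyone is to say that it does not bias the ratio. The cohorts here are formed by a treatment decision, so equality of unrecorded characteristics cannot be assumed. Weights built on recorded variables need not balance the ones the article says are not recorded.

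What is at stake is how the main comparative result is read. The Discussion intends the results to inform policy makers and national antimicrobial programs. A reader who accepts the assurance could give an observed risk ratio more weight than it can bear. The two statements on causality compound this, because the article offers two incompatible interpretations of one estimate and does not say which governs.

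**Working it through.** **No figure to reproduce.** The article attaches no number to the bias, so the check is one of logic, with an illustration on assumed inputs.

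**Step 1: the equal-bias sentence.** Take one unmeasured binary factor that multiplies risk by RRu, with prevalence p1 in the suppressive cohort and p0 in the episodic cohort, and no true effect of treatment. The risk ratio that appears is the bias factor

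B = [1 + (RRu − 1) × p1] / [1 + (RRu − 1) × p0].

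All values of RRu, p1 and p0 below are assumptions. They stand for the imbalance left after weighting on the measured variables.

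| RRu | p1 | p0 | Calculation | B |
|---|---|---|---|---|
| 2 | 0.40 | 0.40 | 1.40 / 1.40 | 1.00 |
| 3 | 0.30 | 0.30 | 1.60 / 1.60 | 1.00 |
| 1.5 | 0.40 | 0.30 | 1.20 / 1.15 | 1.04 |
| 2 | 0.40 | 0.30 | 1.40 / 1.30 | 1.08 |
| 2 | 0.40 | 0.20 | 1.40 / 1.20 | 1.17 |
| 2 | 0.60 | 0.30 | 1.60 / 1.30 | 1.23 |
| 3 | 0.60 | 0.30 | 2.20 / 1.60 | 1.38 |
| 3 | 0.60 | 0.20 | 2.20 / 1.40 | 1.57 |

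When p1 = p0, B is 1.00 whatever the value of RRu, so the factor is not a confounder of this ratio. When p1 and p0 differ and RRu is not 1, B is not 1.00 and nothing cancels it. Every unequal row above has p1 larger than p0. If p1 were smaller, B would fall below 1: swapping 0.40 and 0.20 at RRu = 2 gives 1.20 / 1.40 = 0.86. The formula therefore refutes the assurance, but it does not fix a direction.

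**Step 2: whether the sentence applies to this comparison.** Its subject is the residual confounding named in the sentence before it, and it covers all the included populations. The two cohorts of women with recurrent infections are among those populations, and they are the ones compared by a risk ratio. The descriptive results of WP 1 involve no such contrast, so WP 2 is where the statement matters.

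**Step 3: the two positions on causality.** Set side by side:

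- Statistical Analysis, primary outcome: "marginal structural models will be fitted to estimate causal effects by correcting for confounders".
- Abstract (Conclusions) and Discussion: the study "it will not allow causality analysis".

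A marginal structural model with inverse probability weights has a causal target only if there is no unmeasured confounding. The Discussion says that unmeasured confounding is present. The article does not state the condition under which the first position would hold, so the two cannot both stand as written.

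**The case against.** The strongest reply is that the equal-bias sentence is a remark in the Discussion on which no analysis step rests, and that the authors do not act as if it were true. They go on to promise sensitivity analyses and external adjustment, and to weigh the issue when interpreting results. Most of the article speaks of correlation, and it disclaims causality twice. On this view the causal phrase in the methods is only the customary description of a marginal structural model and is the one expression out of line. This is largely fair, and it limits the consequence. It does not make the sentence correct: the promised analyses would be unnecessary if it were true.

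It could also be argued that the authors meant under-recording that is similar for everyone. The sentence refers to residual confounding, however, and equal under-recording of a factor still leaves confounding if its true distribution differs between cohorts.

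Several stronger readings are tempting, and the documents do not support them:

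- *The risk ratio is biased upward.* Confounding by indication could plausibly push it above 1, but the article gives neither direction nor size.
- *The cohorts differ in severity by design.* Both are made up of women with recurrent infections, and nothing says that suppressive therapy is reserved for the worse cases. The Abstract expects its use to be highly variable.
- *The study expects to find harm from suppressive therapy.* The stated aim is to determine whether there is more or worse infection. The stated expectations concern inadequate management and variable practice.
- *The plan uses the sentence to dismiss the bias.* The mitigation that follows it shows otherwise.
- *The propensity covariates are inadequately specified.* An article may leave that detail to the full protocol or analysis plan.

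**Conclusion.** The point holds in a limited form. The equal-bias sentence is wrong for the WP 2 risk ratio, and the causal aim in Statistical Analysis conflicts with the disclaimers in the Abstract and the Discussion. Both are errors in what the article states. An analysis plan that is not shown could not make the sentence true or reconcile the two positions.

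The size of any bias is unknown. Over the assumed inputs with the factor more common under suppressive therapy, a null risk ratio would appear as 1.04 to 1.57, and as 1.17 in the example of a doubled risk at 40% versus 20%. These values show how the formula behaves and do not estimate this study's bias. The logical conclusion needs no assumption beyond the definition of confounding. It would be the same if the contrast were read as antibiotic exposure versus none, which is how Statistical Analysis words it. No planned number changes, so this is a correction that should be made and not a flaw that invalidates the study.

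**What to change.** 1. Delete the equal-bias sentence. In its place, state that residual confounding, including by indication, may differ between the cohorts and could plausibly move the risk ratio above 1, and that its direction and size are not known.
2. Use one position on causality in the Abstract, Statistical Analysis and Discussion. One suitable wording: associations adjusted for measured confounders; a causal reading requires no unmeasured confounding. If a causal estimand is preferred, state its assumptions and withdraw the blanket disclaimers.
3. Within the sensitivity analyses and external adjustments already promised, commit to a quantitative bias analysis of each primary WP 2 risk ratio, such as an E-value or a table of bias factors over a stated range. A negative-control outcome from the same records is optional.
4. As a suggestion only, outside the error itself: name in the full protocol the measures of prior infection and antibiotic burden before the index date that enter the propensity score.

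The cost is a few sentences and a minor extra analysis. An E-value or bias-factor table needs only the estimated risk ratios and assumed inputs, and a negative control would use records already to be extracted.

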## Appendix

Multimedia Appendix 1 Description of the first phase variables.

## Abbreviations

ATC: anatomical, therapeutic, chemical
CMBD: Conjunt mínim bàsic de dades (Minimum Basic Data Set)
CMBD-HA: Conjunt mínim bàsic de dades a d’hospitalizació d’aguts (Minimum Data Set of Diagnoses at Hospital Discharge)
CMBD-UR: Conjunt mínim bàsic de dades d’atenció urgent (Minimum Data Set of Diagnoses at Emergency Departments)
ICD-10: International Classification of Diseases, 10th Revision
ICS: Institut català de la salut (Catalan Health Institute)
MHDA: Medicació hospitalària de dispensació ambulatòria (Hospital Dispensing Medicines Register)
SIDIAP: Sistema d’informació per al desenvolupament de la investigació en atenció primària (Information System for the Development of Research in Primary Care)
PHC: primary health care
UTI: urinary tract infection
WP: work package
